**Fig. 4 Fig4:**
[figure not shown]
Sequential rollout of the suicide prevention system (shaded cells) to the clusters

In our SWTD, the implementation of SUPREMOCOL is sequentially rolled-out to five clusters, until eventually the system is implemented in the whole province. For this purpose, the province is divided into five sub-areas that are based on the service areas of the five participating SMHI’s. The SMHI and a few participating organizations are exposed to the experimental condition from the start of their cluster, but at various time points, more organizations in that cluster may participate if they sign up for participation [40].

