#### Statistical methods

To examine whether SUPREMOCOL leads to a reduction of completed suicides of 20% in the province of Noord-Brabant, the total number of completed suicides in the post-measurement will be compared to the total number of completed suicides in the pre-measurement. As the total number of residents in this province might have changed, we will also compare the pre- and post-incidence rates of suicides. An exact rate ratio test will be used. To take general trends over time into account, we will compare the incidence ratio in Noord-Brabant with the incidence ratios in other provinces in Noord-Brabant, and with the other provinces combined.

To examine whether SUPREMOCOL leads to a reduction of completed suicides and suicide attempts in association with the stepwise implementation of the system intervention in the subregions of the province, the total number of completed suicides and suicide attempts in each month will be compared to the two levels of our stepped wedge trial: region and time. A poison multilevel model will be used. The occurrence of completed suicide or admissions due to suicide risk in an SMHI will also be taken into account in the analysis. The suicide rates will be corrected for seasonal fluctuations [45]. In a second model, organisational differences between the regions, such as available number of crisis departments, will be taken into account. In a third model, the level of treatment integrity per subregion will be taken into account as well.

To explore whether SUPREMOCOL leads to a reduction of suicidal ideation in people registered in the monitoring system, the scores on the PHQ-9, SIDAS, and decision aid -that will be filled out by participants during the year that they receive the Supremocol additional care- will be compared by repeated measures. This will be used as exploratory process evaluation, as there is no control group for this.

To examine the impact of SUPREMOCOL with regards to reach, efficacy, adoption, implementation, and maintenance, an impact score will be calculated for each SMHI region and time period. This scores will be based on the function of all five RE-AIM dimensions, which are represented on a 0% (no impact) to 100% (best possible impact) scale [43].

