### Potential strengths of the study

This study has three major strengths. First, the stepped wedge trial design combined with the RE-AIM framework is a strength, as it offers multiple benefits for implementation and evaluation. In our opinion, the SWTD is the most ethical design, as all areas act as their own control group, and therefore no areas will be excluded from the suicide prevention system [41], as we believe SUPREMOCOL will have considerable added value to the current care as usual [41, 48]. A stepwise implementation of the intervention is also highly desirable due to scientific and practical reasons [41, 48], as it creates the possibility to control for a time effect by enabling comparison between the old and new organization of health care at the sub-levels of the clusters. Furthermore, implementing the suicide prevention system on a provincial-wide scale at once would be rather impractical and a threat to the feasibility of the project. This stepwise implementation will make the implementation more manageable. The combination with the RE-AIM framework is to our opinion a valuable addition to the SWTD, as it will provide insight into the impact of the intervention. This information is useful in the evaluation of the efficacy of SUPREMOCOL. Moreover, information from the perspective of the stakeholders and about facilitating and hindering factors in implementation could be used to further improve the prevention system.

A second major strength will be that we choose to evaluate the efficacy of the intervention with the outcome parameters completed suicides, suicide attempts, and suicide ideation. This gives direct information about the effectiveness of the intervention, as preventing suicide is the ultimate goal of suicide prevention.

Third, it has been argued that effective action towards reducing suicide would need combined interventions by different providers in multiple domains [29, 30, 49, 50] – so-called multilevel interventions [1, 51]. Therefore, we will not only include (mental) health care institutions but organizations in all other settings that can participate by signaling and registering people at risk for suicide in the monitoring system, which is also considered as a strength of this study [39].

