### Potential limitations of the study

We identified two factors that may form potential limitations of our study. A first potential limitation is that randomization of the starting order of the clusters will not be feasible as the SMHI’s might be in different phases in terms of preparation for implementing the intervention. We identified this potential limitation as there are, for example, changes and shortages in personnel within the crisis care departments of the SMHI’s, which will make the implementation of the intervention a challenge. However, as discussed in previous research, although randomization in stepped wedge trial designs is recommended, the trial might also be performed without, if it is logistically not feasible [52]. Given the vulnerability of our target group, we will not assign clusters to the intervention condition if they are not completely ready, and intervention allocation to the SMHI areas will only be determined based on six criteria indicating the readiness of the SMHI for the implementation.

A second potential limitation is that SUPREMOCOL is not the only suicide prevention initiative that residents in Noord-Brabant are exposed to. For example, as gatekeepers training has gained increased attention in the Netherlands, (mental) health care professionals and other participating chain partners might have increasing awareness to and better screening skills for screening suicide risk. This might be beneficial for the clusters that start the implementation of SUPREMOCOL on a later moment. Another example is that some of the participating organizations operate in the whole province, such as the railway services. In these organizations, the same professionals will participate during the whole duration of our trial, only the geographical areas that are exposed to the intervention will expand. It is possible that they will be better trained in delivering the intervention in the last period of the SWTD, in comparison to period one, which is also advantageous for clusters that start on a later moment. Although this might be beneficial for our outcomes, it might also bias our results.

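### The stepped wedge Poisson model names time only as a level beside region; fitted that way, about half of any province-wide trend would be credited to SUPREMOCOL, so a fixed calendar-time effect should be stated

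*Protocol article*

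**What the plan says.** Under Statistical methods, the stepped wedge analysis takes monthly counts of suicides and attempts, which "will be compared to the two levels of our stepped wedge trial: region and time". The model is named next: "A poison multilevel model will be used". Two adjustments follow for the first model: "The occurrence of completed suicide or admissions due to suicide risk in an SMHI will also be taken into account in the analysis", and "The suicide rates will be corrected for seasonal fluctuations". A second model adds organisational differences between regions, and a third adds treatment integrity.

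The one explicit step against secular trends stands in the preceding paragraph and belongs to the pre-post comparison: "To take general trends over time into account, we will compare the incidence ratio in Noord-Brabant" with that in other provinces.

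Under Stepped wedge trial design, "the implementation of SUPREMOCOL is sequentially rolled-out to five clusters". Potential strengths of the study gives control of time as a reason for the design: "it creates the possibility to control for a time effect by enabling comparison between the old and new organization of health care". Potential limitations of the study expects gatekeeper training to spread during the roll-out and adds: "This might be beneficial for the clusters that start the implementation of SUPREMOCOL on a later moment".

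**The concern.** In a stepped wedge, intervention status rises with calendar time in every region. The design protects against a shared trend only if the model compares regions that have crossed over with regions that have not, at the same time. A fixed effect for each period does this. A level in a multilevel model does not do it reliably. If time is the occasion level, nothing in the mean model carries a trend. If time is a random effect, its estimates are shrunk towards zero.

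None of the listed adjustments takes over that role. Season repeats each year. Organisational differences describe regions. Integrity describes how well the intervention is delivered. Suicides and admissions within the institution are not a calendar term, and how much trend they would absorb is unknown.

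At stake is hypothesis 2 for both outcomes. A shared fall could be reported as benefit; a shared rise could mask benefit or look like harm. Attempts are the more exposed outcome, because they are evaluated only in the stepped wedge and have no comparison with other provinces behind them. Randomisation of the starting order is itself conditional (Allocation).

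**Working it through.** The protocol gives no calculation for the stepped wedge model. Its 184 events a year belong to the pre-post comparison, so there is no figure to reproduce here.

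**Inputs.** Five regions, one crossing over per period (Stepped wedge trial design). Periods 0 to 5 of three months each (Public health impact), hence 18 months. 365 suicides in 2017 (Sample size) and 293 in 2014 (Background). Assumed: equal regions, log-linear province-wide trend, no overdispersion, no true effect unless stated, two-sided 5%. Events per region-period: 365 × 1.5 / 30 = 18.25, or about 6 per region-month.

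**1. How much trend enters without a time term.** A region crossing over at period c has control periods centred at (c − 1)/2 and intervention periods centred at (c + 5)/2. The gap is 3 periods, or 9 months, in every region. The within-region contrast therefore picks up 9/18 = 50% of the trend. If the region variance is estimated at zero and regions are pooled, the gap is 17.5/7.5 = 2.33 periods, or 7 months (39%). Here 17.5 = 55 − 15 × 2.5 is the cross-product of intervention with period, and 7.5 = 15 − 15²/30 is the sum of squares of the intervention indicator.

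**2. Standard error of the log rate ratio, 1/√(18.25 × SS).**
- Pooled: SS = 7.5, SE = 0.085.
- Region effects: SS = 7.5 − (55/6 − 7.5) = 5.833, SE = 0.097.
- Region and fixed period effects: SS = 5.833 − (55/5 − 7.5) = 2.333, SE = 0.153.

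**3. False rejection, Φ(b/SE − 1.96) + Φ(−b/SE − 1.96).**
- *20% fall over 18 months:* b = 0.5 × 0.2231 = 0.112, rate ratio 0.894, b/SE = 1.15, rejection 21%.
- *20% fall in a year:* b = 7/12 to 9/12 of 0.2231 = 0.130 to 0.167, rate ratio 0.88 to 0.85.
- *The protocol's own pace:* (365/293)^(1/3) = 1.076 a year, log 0.0732. b = 0.043 to 0.055, b/SE = 0.50 to 0.57, rejection 8-9%.
- *Attempts at that pace, volumes assumed:* the SE scales by √(365/N). Pooled, 1,500 a year gives 0.0422 and 17%; 3,000 gives 0.0298 and 30%.

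**4. Simulation, including time as a random effect.**

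| Scenario, no true effect | No time term, season only or random time | Fixed periods |
|---|---|---|
| Suicides, 20% fall over 18 months | rate ratio 0.89, rejects 19-21% | 1.006, 4% |
| Suicides, 20% fall a year | rate ratio 0.86-0.90, rejects 24-32% | about 1.01, 5-6% |
| Suicides, 7.6% a year, either direction | rejects 7-9% | 4-6% |
| Attempts, 1,500-3,000 a year, 7.6% a year | rejects 15-33% | about 5% |

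A random time effect barely helps at these counts: for the 20% fall over 18 months the rate ratio is 0.892 with season only and 0.894 with random time plus season. With ten times the events it still credits 35% (period) to 48% (month) of the trend. With one or four post-roll-out periods, or a 12-month period 0, random time plus season credits 45-51% and rejects in 17-31%.

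**5. With a true 20% reduction and a 7.6% yearly rise.** 0.80 × e^0.043 = 0.835 and 0.80 × e^0.055 = 0.845; simulation gives 0.83-0.84 in place of 0.80.

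**6. Power with fixed periods.** 0.2231/0.153 = 1.46, and Φ(1.46 − 1.96) = 31%; slightly less once the reduction itself lowers the counts. So about 30%.

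**The case against.** The strongest reply is that the text never calls time a random effect. The sentence is loosely worded, and its two levels may simply mean the two dimensions of the design, cluster and period. Potential strengths of the study shows that control of time is intended. Fixed periods are thus compatible with the text, and an analysis plan could specify them. This stands: the bias is conditional on how time is fitted and is not established by the wording alone. It does not remove the point, because the section goes as far as naming the levels, the covariates and a sequence of three models, and time appears in it only as a level and as season.

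The large error rates need a steep trend. The protocol's counts show a rise over three years, not a fall within one; at that pace the effect on suicides is small. The figures for attempts rest on assumed volumes. Both objections stand.

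The simulated models also leave out the term for suicides and admissions within the institution.

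Finally, the railway example under Potential limitations of the study describes staff who deliver the intervention better with time. That is a growing intervention effect, not a shared trend, and common period effects would not remove it.

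**Conclusion.** The concern holds in a conditional form. Fitted as an occasion level or random effect, time would leave about half of the start-to-end province-wide trend in the intervention estimate (39% if the region variance is estimated at zero). False rejection for suicides would be about 20-32% under a strong trend and 7-9% at the protocol's own pace; for attempts it would be about 15-33% at the assumed volumes. These figures rest on equal regions, a log-linear trend and no overdispersion.

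Three stronger readings are not supported. A reader might infer that the plan ignores time, but time is named and its control is intended. A reader might infer that a trend would be credited to SUPREMOCOL mostly or entirely; the share is about half. A reader might infer that the test of the 20% hypothesis is compromised, but that test is the pre-post comparison, which has its own comparison with other provinces. Only hypothesis 2 is affected.

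**What to change.** State under Statistical methods that all three stepped wedge models, for suicides and for attempts, include calendar time as a fixed effect common to all regions, with one term per three-month period or per month. The intervention effect is then the contrast, at the same time, between regions that have and have not crossed over. Fixed month effects make the season correction redundant; with period effects, keep season only where it still varies within periods. A linear time term also removed the bias in simulation, but the trend simulated was log-linear; categorical terms do not need that assumption.

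No new data are needed. The cost is precision: the standard error for suicides rises from about 0.10 to about 0.15, and power for a 20% reduction in the stepped wedge analysis is about 30%. The lost precision came from the comparison confounded with time. The protocol should acknowledge this power, and should say that common period effects do not deal with an intervention effect that grows during the roll-out.

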## Background

Completed suicides and suicide attempts c physical and emotional harm on the individual. Significant others, the community, and even entire nations suffer the consequences of such tragic events [1, 2]. Annually, more than 800,000 suicides occur worldwide, of which over 56,000 were reported in the European Union (EU), and almost 2000 in the Netherlands [1, 3, 4]. Although suicide rates in the Netherlands were equal to the EU-average [3], they did show a sharp incline of 37% between 2007 and 2013 [4]. This might be related to the economic recession in 2008 and rigorous budget cuts in the mental health sector [5, 6]. Since 2013, the relative suicide rate in the Netherlands has been stable, without decreasing [4]. In Noord-Brabant, one of the twelve provinces of the Netherlands, this stabilization in the suicide rates did not take place, as the absolute number of suicide in this province increased by 64%. Remarkably, 30% of this 64% increase in completed suicides happened in the years after 2013 [4]. At the start of the grant application for this study in 2015, Noord-Brabant even ranked second nationally over the five previous years (2010–2014) and there were 293 suicides in 2014, which is 11,5 suicides per 100,000 residents [4]. This poses a problem in the Netherlands and more specifically a regional problem in Noord-Brabant.

An important issue in effective suicide prevention is that approximately two-thirds of suicide victims were not receiving mental health care [7, 8], while they were probably in need of it, as suicide occurs mostly in the context of mental disorders [1, 2]. This might be due to a lack of visibility of people at risk, as help-seeking behaviour for suicidality is low, possibly due to stigma and poor suicide literacy [9]. Moreover, transitions of and discharges from care are associated with an increased risk of suicide attempt or death [10, 11]. An exploration amongst stakeholders identified that a tentative explanation might be a lack of communication between health care providers of different institutions or lack of swift entry into specialist care due to logistical barriers and waiting lists.

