### Primary outcome: completed suicides

The primary outcome of this study is completed suicides. In the Netherlands, the occurrence of completed suicide is registered by coroners in the ORION system. The records from the ORION system regarding Noord-Brabant will be obtained from the Regional Public Health Institutes (PHI [in Dutch: Gemeentelijke Gezondheidsdienst; GGD]): GGD Brabant-Zuidoost, GGD West-Brabant, and GGD Hart voor Brabant. The PHI’s report their records to Statistics Netherlands, who collect the records for the whole country and make corrections if needed. To evaluate whether SUPREMOCOL leads to a reduction of completed suicides of 20% in the province of Noord-Brabant (hypothesis 1), completed suicides will be assessed during a one-year pre-post measurement for the total population of the province of Noord-Brabant. The pre-measurement will take place in the year before any of the areas in Noord-Brabant have entered the roll-out period (thus: 1 year before the start of period 1 of the SWT; therefore including period 0 of the SWT), and the post-measurement will take place in the year after implementation in all areas (thus: after period 5 of the SWT). National records from Statistics Netherlands will also be used for the pre-post evaluation, as completed suicide rates will be compared in time (pre-post) and per region (Noord-Brabant versus other provinces in the Netherlands). As it is also hypothesized that SUPREMOCOL leads to a reduction of completed suicides and suicide attempts in association with the stepwise implementation of the system intervention in the subregions of the province (hypothesis 2), completed suicides will also be assessed during the stepped wedge trial in the subregions of Noord-Brabant. Regional PHI records will be used for the SWT evaluation. For this, the total number of completed suicides per month will be examined.

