### Exploratory process measure: suicidal behaviour in SMHI patients

Suicidal behaviour in SMHI patients will be measured and taken into account in the analysis of the stepped wegde trial. It will be measured by SMHI records about the number of completed suicides among their patients and admissions into their institution due to suicide risk. The measurement period will take place during the stepped wedge trial and will be collected for each SMHI.

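### The stepped wedge analysis appears to adjust for suicides and suicide-risk admissions among SMHI patients, which are partly the outcome and partly consequences of the intervention, so the rate ratio for hypothesis 2 is open to bias in either direction

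*Protocol article*

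**What the plan says.** The Statistical methods section compares monthly totals of completed suicides and attempts across region and time and names the model: "A poison multilevel model will be used" (a Poisson model is meant). It then adds: "The occurrence of completed suicide or admissions due to suicide risk in an SMHI will also be taken into account in the analysis". Only after this come the second model, "In a second model, organisational differences between the regions, such as available number of crisis departments, will be taken into account", and a third model with treatment integrity.

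The section on suicidal behaviour in SMHI patients, headed as an exploratory process measure, repeats the intention: "Suicidal behaviour in SMHI patients will be measured and taken into account in the analysis of the stepped wegde trial". It defines the variable, "It will be measured by SMHI records about the number of completed suicides among their patients and admissions into their institution due to suicide risk", and its timing: "The measurement period will take place during the stepped wedge trial and will be collected for each SMHI".

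The stepped wedge outcome is set in the section on the primary outcome: "For this, the total number of completed suicides per month will be examined". SMHI patients are not excluded from that count.

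**The concern.** There are two problems with using these variables as covariates.

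- **Part of the outcome.** Clusters are SMHI service areas and the outcome is every suicide in the area. Suicides among the SMHI's patients living there are a subset of that outcome. A model with the total on the left and a part of it on the right no longer estimates the effect on the total.
- **Consequence of the intervention.** Pillar 2 is swift access to the SMHI, and Table 2 lists admissions arranged by SMHI professionals as an implementation measure for that pillar. In a cluster that has crossed over, both SMHI suicides and admissions are measured after the intervention has begun to act on them. Nothing in the article limits them to values before rollout.

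At stake is the intervention rate ratio for hypothesis 2. This is the analysis that the Discussion credits with controlling for time effects.

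**Working it through.** **Plan's own figure.** The protocol gives no figure for the stepped wedge model. Its 184 events per year belong to the pre-post comparison and do not bear on this point.

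**Inputs from the protocol.** Five clusters; three-month periods, with periods 0 to 5 giving 18 months; 365 suicides in 2017, so 365 / (5 × 12) = 6.08 per cluster-month if clusters are equal; target reduction 20%, so a true rate ratio of 0.80.

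**Assumptions.** Clusters are of equal size and the full effect starts at crossover. The share *s* of suicides among SMHI patients is not given. The Background says "approximately two-thirds of suicide victims were not receiving mental health care", so one-third is taken as a proxy, with a range of 0.2 to 0.5. That figure covers any mental health care, not SMHI care alone.

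**Approximation.** Total = SMHI suicides + other suicides. Holding SMHI suicides at their level before the intervention, the model sees only the change in the others:

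adjusted RR ≈ *s* + (1 − *s*) × RR(others)

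true RR = *s* × RR(SMHI) + (1 − *s*) × RR(others)

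**Simulation.** Poisson regression with cluster and period effects and an intervention indicator, with and without monthly SMHI suicides as a covariate (3,000 trials per scenario). The true RR is 0.80 in every row.

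| Scenario | s | RR(SMHI) | RR(others) | Approximate adjusted RR | Simulated, no covariate | Simulated, with covariate |
|---|---|---|---|---|---|---|
| Uniform | 0.2 | 0.80 | 0.80 | 0.2 + 0.8 × 0.8 = 0.84 | 0.80 | 0.83 |
| Uniform | 1/3 | 0.80 | 0.80 | 1/3 + 2/3 × 0.8 = 0.87 | 0.80 | 0.86 |
| Uniform | 0.5 | 0.80 | 0.80 | 0.5 + 0.5 × 0.8 = 0.90 | 0.80 | 0.89 |
| SMHI suicides unchanged | 1/3 | 1.00 | 0.70 | 1/3 + 2/3 × 0.7 = 0.80 | 0.80 | 0.80 |
| SMHI suicides up 20% | 1/3 | 1.20 | 0.60 | 1/3 + 2/3 × 0.6 = 0.73 | 0.80 | 0.74 |

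Without the covariate the model recovers 0.80 throughout. With it, the uniform case at one-third loses 1 − ln 0.86 / ln 0.80 = 1 − 0.151 / 0.223 = 32% of the log effect. The last row exaggerates the effect.

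**Admissions.** Assume 10 admissions per cluster-month, raised 1.5-fold by the intervention, and again a true RR of 0.80. The adjusted RR is 0.89 if half the effect runs through admissions and 1.00 if all of it does. It is 0.64 if admissions carry none of the effect and only track underlying monthly risk. The admission rate and its change are illustrative, as the protocol gives neither.

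**Precision.** The standard error of the log rate ratio without the covariate is about 0.163. At a true RR of 0.80 the unadjusted model reaches two-sided 5% significance in about 28% of simulated trials. With the covariate, at one-third and a uniform effect, it does so in about 10%.

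**The case against.** **The wording does not settle that these are covariates.** The section on suicide attempts uses the same phrase, *taken into account*, for attempts and ideation, which are analysed in their own right. SMHI suicidal behaviour is also headed as an exploratory process measure. If it is only a separate outcome, no bias arises. This stands as a reason for moderate confidence. It does not remove the point: within the Statistical methods section the phrase introduces the adjustment variables of the second and third models, and the sentence sits directly after the main model. An analyst following it could reasonably fit the biased model. Nor is this a detail merely left to an analysis plan, since the article states the intention in two places.

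**The direction is not fixed.** A reader might infer that the adjustment must remove part of the effect and pull the ratio towards 1. That needs SMHI suicides to fall. The intervention is meant to find people outside care and bring them into the SMHI, which enlarges the patient population in which SMHI suicides are counted. Those suicides may then stay level or rise, and the bias vanishes or reverses. This objection stands.

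**The main test is elsewhere.** The 20% target, the sample size and the exact rate ratio test all belong to the province-wide pre-post comparison, which does not use these variables. This also stands and limits the severity.

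**Attempts.** The subset argument does not apply to suicide attempts. For that outcome only the objection to adjusting for consequences of the intervention remains.

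**Conclusion.** The concern holds for the stepped wedge analysis. On the natural reading, the first effect model conditions on a component of its own outcome and on variables that the intervention can change, so the rate ratio for hypothesis 2 is biased. With a true ratio of 0.80, a one-third SMHI share and the stated design assumptions, the adjusted ratio is about 0.86 under a uniform effect (roughly 0.83 to 0.89 for shares of 0.2 to 0.5), 0.80 if SMHI suicides are unchanged and 0.74 if they rise by 20%. For admissions, too, the sign is open.

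A reader might also infer that hypothesis 2 would fail because of this covariate. The figures do not support that as a general statement: even the unadjusted model has only about 28% power at 0.80 under these assumptions, so a non-significant result is likely either way. Hypothesis 1 is unaffected.

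Severity: should be fixed. Confidence: moderate, because the protocol does not define how the variables enter the analysis.

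**What to change.** State in the Statistical methods section, and in the section on suicidal behaviour in SMHI patients, that:

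1. SMHI suicides and suicide-risk admissions recorded during the trial are not covariates in any stepped wedge effect model for completed suicides or attempts.
2. They are reported as separate exploratory process outcomes, using the same region-and-time model.
3. If adjustment for differences between SMHIs is wanted, only each region's level before rollout is used.

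The cost is wording only. The planned data are still collected and reported. Pre-rollout adjustment, if chosen, uses SMHI records from period 0.
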